#### Adverse events include:

- The exacerbation of a pre-existing pathology;
- An increase in the frequency or intensity of an episodic event or pre-existing condition;
- A condition occurring or diagnosed after the administration of the study drug, even if current before the start of the study;
- Persistent diseases/symptoms at the baseline visit that worsen after the start of the study.

#### Adverse events do NOT include:

- Medical or surgical procedures (e.g. surgery, endoscopy, tooth extraction, transfusions), but the condition requiring the procedure is an adverse event
- Diseases or conditions present at the beginning of the study that have not worsened, but remained stable during the course of the study.

- Situations in which no unexpected adverse event has occurred (e.g. hospital admission for elective cosmetic surgery/social problems).
- An overdose of antiviral agents or concomitant drugs without onset of symptoms or associated signs.
- Laboratory abnormalities deemed by the investigator to be of no clinical significance.

Adverse events will be graded according with CTCAE v5.0. (Appendix B) Grade 1 and Grade 2 events are not considered adverse events, but details of these events must be documented in detail in the subject's study files.

Stable chronic conditions which are present prior to clinical trial entry and do not worsen are not considered adverse events and will be accounted for in the subject's medical history.

**Serious Adverse Events (SAE's).** A 'serious adverse event' is defined in Article 2(o) of Directive 2001/20/EC as follows: 'Any untoward medical occurrence or effect that at any dose results in death, is life-threatening, requires hospitalization or prolongation of existing hospitalizations, results in persistent or significant disability or incapacity, or is a congenital anomaly or birth defect'. These characteristics/consequences have to be considered at the time of the event. For example, regarding a life-threatening event, this refers to an event in which the subject was at risk of death at the time of the event; it does not refer to an event which hypothetically might have caused death if it were more severe. Some medical events may jeopardize the subject or may require an intervention to prevent one of the above characteristics/consequences. Such events (hereinafter referred to as 'important medical events') should also be considered as 'serious' in accordance with the definition. Medical and scientific judgement should be exercised in deciding whether an event is 'serious' in accordance with these criteria

A Serious Adverse Event is defined as an SAE meeting one of the following:

- Death during the period of protocol-defined surveillance
- Life Threatening Event (defined as a participant at immediate risk of death at the time of the event)
- In-patient hospitalization or prolongation of existing hospitalization during the period of protocol-defined surveillance

- Results in congenital anomaly or birth defect
- Results in a persistent or significant disability/incapacity

Any other important medical event that may not result in one of the above outcomes, may be considered a serious adverse experience when, based upon appropriate medical judgment, the event may jeopardize the participant and may require medical or surgical intervention to prevent one of the outcomes listed above.

**AE/SAE relationship assignment.** For all collected AE's/SAE's, the clinician who examines and evaluates the subject will determine the adverse event's causality based on temporal relationship and his/her clinical judgment. The degree of certainty about causality will be graded using the categories below:

- **Definitely Related:** There is clear evidence to suggest a causal relationship, and other possible contributing factors can be ruled out. The clinical event, including an abnormal laboratory test result, occurs in a plausible time relationship to drug administration and cannot be explained by concurrent disease or other drugs or chemicals. The response to withdrawal of the drug (de-challenge) should be clinically plausible. The event must be pharmacologically or phenomenologically definitive, with use of a satisfactory rechallenge procedure if necessary.
- **Probably Related:** There is evidence to suggest a causal relationship, and the influence of other factors is unlikely. The clinical event, including an abnormal laboratory test result, occurs within a reasonable time sequence to administration of the drug, is unlikely to be attributed to concurrent disease or other drugs or chemicals, and follows a clinically reasonable response on withdrawal (de-challenge). Re-challenge information is not required to fulfill this definition.
- **Possibly Related:** There is some evidence to suggest a causal relationship (e.g., the event occurred within a reasonable time after administration of the trial medication). However, the influence of other factors may have contributed to the event (e.g., the subject's clinical condition, other concomitant events). Although an adverse drug event may rate only as "possibly related" soon after discovery, it can be flagged as requiring more information and later be upgraded to "probably related" or "definitely related", as appropriate.

- Unlikely: A clinical event, including an abnormal laboratory test result, whose temporal relationship to drug administration makes a causal relationship improbable (e.g., the event did not occur within a reasonable time after administration of the trial medication) and in which other drugs or chemicals or underlying disease provides plausible explanations (e.g., the subject's clinical condition, other concomitant treatments).
- Not related: The AE is completely independent of study drug administration, and/or evidence exists that the event is definitely related to another etiology. There must be an alternative, definitive etiology documented by the clinician.

**SAE reporting procedures.** The information to be reported for each SAE is: the date of event occurrence, the date of event resolution, a brief description of the event, concomitant therapy, lab test reports, maximum intensity of the event or correlation with the agent. If there is any change in the information over time, an updated SAE report must be sent. All adverse reactions simultaneously defined as serious and unexpected must be reported by the investigator to the study sponsor as soon as possible.

The investigator will report all SAE to Eudravigilance through the specific form, to Ethical Committees, and to the manufacturer, within the timelines of the article 17 of the European Directive 2001/20/EC. The investigator will provide an annual Development Safety Update Report, including all Serious Adverse Events occurring in the Study, to the Regulatory Agency, and to the Ethical Committee as per local requirements.

Notification deadlines:

- if, in addition to being serious and unexpected, a SAE is also fatal or life-threatening, a preliminary SAE report must be completed as soon as possible and, in any case, within 24 hours after being informed about the event.
- For all other serious and unexpected adverse events, the investigator must complete a SAE report as soon as possible after the manifestation of the event and, in any case, no later than 15 days after becoming aware of the event.

**Monitoring of AE'S/SAE'S.** Any AE that occurs between the times a study participant signs the informed consent form and the time s/he departs the study at the end of the final follow-up visit (or at the time of

early discontinuation of the subject from the study for any reason) will be captured and recorded. At each contact with the subject, the investigator (or designate) must seek information on adverse events by specific questioning and, as appropriate, by examination.

All AEs and SAEs must be followed up:

- until their complete resolution
- until their stabilization
- until the event can be attributed a new etiology
- until the patient ceases to be in the care of the Centre

The investigator must ensure that the follow-up reports include all supplementary information allowing a complete evaluation of the nature and/or the cause-effect relationship of the AE or SAE, including further laboratory and other tests, pathology reports, and any specialist examinations.

**Suspected unexpected serious adverse reactions (SUSARS).** The investigator shall ensure that all relevant information about suspected serious unexpected adverse reactions that are fatal or life-threatening is recorded and reported as soon as possible to the Database Eudravigilance, and to the Ethics Committee, and in any case no later than seven days after knowledge by the sponsor of such a case, and that relevant follow-up information is subsequently communicated within an additional eight days.

All other suspected serious unexpected adverse reactions shall be reported to the database Eudravigilance concerned and to the Ethics Committee concerned as soon as possible but within a maximum of 15 days of first knowledge by the sponsor. The sponsor shall also inform all investigators.

Adverse reaction — causality An adverse reaction' is defined in Article 2(n) of Directive 2001/20/EC as follows: 'all untoward and unintended responses to an investigational medicinal product related to any dose administered'. The definition covers also medication errors and uses outside what is foreseen in the protocol, including misuse and abuse of the product. The definition implies a reasonable possibility of a causal relationship between the event and the IMP. This means that there are facts (evidence) or arguments to suggest a causal relationship.

Unexpected' adverse reaction - Definition: Article 2(p) of Directive 2001/20/EC defines 'unexpected adverse reaction' as follows: 'an adverse reaction, the nature or severity of which is not consistent with the applicable product information (e.g. investigator's brochure for an unauthorised investigational product or summary of product characteristics for an authorised product)'.

The term 'severity' is used here to describe the intensity of a specific event. This has to be distinguished from the term 'serious'. Reports which add significant information on the specificity, increase of occurrence, or severity of a known, already documented serious adverse reaction constitute unexpected events

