### Secondary outcomes

- Decreased viral load on nasopharyngeal swab (days 6, 9 and 14)
- Decreased viremia at day 6 and 9
- Increased antibody titre against SARS-CoV2 (days 30 and 60)
- Proportion of patients with negative of SARS-CoV2 nasopharyngeal swab (day 60)
- Length of hospital stay
- Mortality rate at day 28
- Total plasma related adverse event (Febrile reactions, TRALI, TACO, TTI) (day 60)
- Total non-plasma related adverse events (day 60)
- Severe adverse events (SAE) (day 60)

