## APPENDIX B

### ADVERSE/SEVERE ADVERSE EVENT: DEFINITIONS AND MANAGEMENT

**Adverse Events** An ‘adverse event’ is defined in Article 2 (m) of Directive 2001/20/EC as follows: ‘Any untoward medical occurrence in a patient or clinical trial subject administered a medicinal product and which does not necessarily have a causal relationship with this treatment’. An adverse event can therefore be any unfavorable and unintended sign (including an abnormal laboratory finding, for example), symptom or disease temporally associated with the use of a medicinal product, whether or not considered related to the medicinal product

An “adverse event” is any worsening in the general condition of a subject, or a subject participating in a clinical experiment to whom a pharmaceutical product is administered, regardless of its relationship with the given treatment. An AE may also be any unexpected adverse sign (which can include an abnormal laboratory result of clinical significance), and each symptom or pathology temporarily associated with the use of a pharmaceutical product, regardless of its relationship with the same product. AEs may be **expected** (consistent with the information leaflet provided with the product) or **unexpected** (inconsistent with the information available).

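### Appendix B rules Grade 1 and 2 events out of the adverse-event definition, contradicting its own definition and turning the Phase III total adverse-event outcomes into Grade 3 or higher counts

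*Protocol*

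**What the plan says.** Appendix B gives two definitions of an adverse event. The first, taken from the European Directive, covers "Any untoward medical occurrence in a patient or clinical trial subject administered a medicinal product"; the second covers "any worsening in the general condition of a subject". Neither has a severity threshold.

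Later in the same appendix, at the end of the list of what adverse events do not include, the protocol says that "Adverse events will be graded according with CTCAE v5.0" and then that "Grade 1 and Grade 2 events are not considered adverse events". The same sentence adds that "details of these events must be documented in detail in the subject's study files".

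Under Outcomes and endpoints, the Phase III secondary outcomes include "Total plasma related adverse event (Febrile reactions, TRALI, TACO, TTI) (day 60") and "Total non-plasma related adverse events (day 60"). Neither has a grade limit. The line after that list refers the reader to Appendix C for the adverse-event definitions. Appendix C holds the WHO ordinal scale; the definitions are in Appendix B.

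**The concern.** A scale used to grade adverse events cannot also have its two lowest grades declared not to be adverse events, unless the definition itself carries that threshold. Here it does not.

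The clash reaches named outcomes. Read through Appendix B, each total becomes a count of Grade 3 or higher events under a label that says otherwise. Read at face value, each is a count of all grades. Two centres could each follow the protocol and return different totals.

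The data at stake are the reactions the protocol itself expects. The benefit/risk section puts allergic or febrile reaction among the most frequent plasma risks. The trial design section says that safety data in patients at an earlier stage of disease are lacking.

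**Working it through.** The protocol states no figure for this point that could be reproduced. The check is mainly a comparison of texts, followed by an illustration of size.

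**Texts side by side**

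1. *Definition against exclusion (both Appendix B).* Any untoward occurrence, or any worsening, is an adverse event; a Grade 1 or 2 event is not. These two statements conflict directly.
2. *Exclusion against outcomes.* The Phase III totals have no grade limit, and febrile reactions are named without one. Allergic reactions are not named in that outcome; they enter through the word total and through the risk list in the benefit/risk section.
3. *What follows from not being an adverse event.* In Appendix B, causality is assigned for collected AEs and SAEs (AE/SAE relationship assignment). Capture covers "Any AE that occurs between the times a study participant signs the informed consent form" up to the end of follow-up, and follow-up is required for AEs and SAEs (both under Monitoring). A Grade 2 febrile reaction therefore needs no relatedness assessment, and without one it cannot reliably be classed as plasma-related later. The capture rule is not separate evidence of a contradiction, because it applies to whatever counts as an AE. It shows only what the exclusion removes.
4. *Exclusion against seriousness.* Appendix B defines an SAE by its consequence, not its grade. A Grade 2 event that prolongs hospitalization would be an SAE but not an adverse event.

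**Illustration, Phase III, arm A**

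Inputs:
- 91 patients per arm (Sample size, Phase III)
- 3 plasma infusions per arm A patient (Interventions)
- allergic or febrile reaction rate of 1 in 100 (Benefit/risk assessment), with no statement of whether this is per infusion or per patient
- share s of reactions that are Grade 1 or 2: not in the protocol, assumed to be 50% to 90%

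Expected reactions = m × 0.01, where m is 91 × 3 = 273 infusions or 91 patients. Expected counted reactions = m × 0.01 × (1 − s). Chance of at least one counted = 1 − (1 − 0.01 × (1 − s))^m.

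| Rate read as | All grades | Counted, s = 50% | Counted, s = 90% |
|---|---|---|---|
| per infusion (m = 273) | 2.73 | 1.37 | 0.27 |
| chance of at least one | 0.94 | 0.75 | 0.24 |
| per patient (m = 91) | 0.91 | 0.46 | 0.09 |
| chance of at least one | 0.60 | 0.37 | 0.09 |

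**The case against.** The strongest reply is that nothing is lost. The sentence that excludes Grade 1 and 2 events also requires them to be documented, and the plasma-related outcome names febrile reactions without a grade, so a specific outcome could be read as overriding a general appendix rule. Part of this stands: the events are kept at source, and a reader who infers that they go unrecorded goes further than the text. But being kept in the study files is not the same as being assessed for causality, followed up and counted. That the outcome can be read two ways is the defect, not a defence.

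Other stronger readings are also tempting, and the documents do not support them:

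- *That Phase II would probably report no plasma reactions.* The adverse-event totals are Phase III outcomes, and Phase II lists none. Even as arithmetic it does not hold throughout. With 57 × 3 = 171 infusions at 1 in 100 and half of the reactions Grade 1 or 2, the chance of counting none is 0.995^171 = 0.42.
- *That the comparison is biased in favour of plasma.* Only arm A is transfused, so the plasma-related total has no control counterpart; what is shown is an under-counted rate in one arm. For non-plasma events the same exclusion applies in both arms, and no direction is shown.
- *That the safety stopping rule is undermined.* It counts severe events connected with plasma, so excluding Grade 1 and 2 events should change it little if at all.

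It is also fair to say that table layout can be left to the SAP. What counts as an adverse event is different: the protocol fixes it here, and fixes it inconsistently.

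**Conclusion.** The point holds as an internal contradiction between the definition and the exclusion in Appendix B, with a direct effect on two Phase III secondary outcomes. Followed as written, both totals are Grade 3 or higher counts.

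The conclusion rests on the wording. The size depends on two things the protocol does not give: the unit of the 1 in 100 rate and the share of reactions that are Grade 1 or 2. Over the assumed 50-90%, half to nine tenths of the expected allergic or febrile reactions fall out, which is between about 0.5 and 2.5 events in arm A (0.91 − 0.46 = 0.45 at the lower end, 2.73 − 0.27 = 2.46 at the upper). No figure is available for the loss among non-plasma events.

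The primary endpoint is not affected. This is a should-fix.

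**What to change.** Remove the sentence that excludes Grade 1 and 2 events. If a grade threshold is wanted for reporting, state it in the reporting procedures of Appendix B only, so that it does not redefine an adverse event.

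State that the plasma-related and non-plasma-related totals in the Phase III secondary outcomes count events of every CTCAE grade, with causality assigned, and show Grade 3 or higher separately. Correct the cross-reference after those outcomes so that it points to Appendix B.

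The cost is some added eCRF entry and causality assessment for Grade 1 and 2 events, whose details must already be documented. The change should be made prospectively, because causality that was not assessed at the time can be recovered only in part.

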## APPENDIX C

### WHO ORDINAL SCALE FOR ASSESSING PROGRESSION OF PNEUMONIA

1 = Death;

2 = Hospitalized, on invasive mechanical ventilation or extracorporeal membrane oxygenation (ECMO);

3 = Hospitalized, on non-invasive ventilation or high flow oxygen devices;

4 = Hospitalized, requiring supplemental oxygen;

5 = Hospitalized, not requiring supplemental oxygen;

6 = Not hospitalized

1. Coronavirus disease (Covid-19) R&D. Geneva: World Health Organization

<https://www.who.int/blueprint/priority-diseases/key-action/novel-coronavirus/en/>

APPENDIX D

Gantt diagram

[figure not shown]

APPENDIX E.

LIFESAVER – Study flow chart

[figure not shown]

Blood Bank : Convalescent Plasma collection flow chart

[figure not shown]

Supplement: Supplementary file 1 — Additional file 1:. Full study protocol [file 13063_2020_4821_MOESM1_ESM.pdf]
